## *Handling of Withdrawals*

In accordance with the current revision of the Declaration of Helsinki and local Authority regulations at the corresponding countries, a subject has the right to withdraw from the study at any time, for any reason, without prejudice to his future medical care by the physician or the institution. The investigator and the sponsor also have the right to withdraw subjects from the study in the event of serious adverse events, protocol departure, or other reasons. Should a subject (or the subject’s legally authorized representative) decide to withdraw, all efforts will be made to collect and report the final visit observations, and the reasons for withdrawal, as thoroughly and timely as possible.

Withdrawals will be recorded, analyzed and reported to the local Ethical Committee.

5. MATERIALS

## 5.1 Product Name

PrePex

## 5.2 Intended Use

The PrePex device is intended to be used in a medical procedure to compress the foreskin of the penis to allow circumcision of an adult male.

## 5.3 Product Description

The PrePex device contains the following items:

1. A Placement Ring (O-Ring Introducer) made of medical grade biocompatible plastic polymer that is highly used in the medical device industry
2. An Inner Ring made of medical grade biocompatible plastic polymer
3. An O-Ring made of medical grade biocompatible elastic material
4. Verification thread

The use of the PrePex device should follow the Instruction for Use supplied by Circ MedTech and following an appropriate formal PrePex training course in a center of excellence located in Kigali, Rwanda, to the operator.

## 5.4 Identification of the Investigational Medical Devices

The label includes trade name and address of the manufacturer, batch code and all other essential information. Devices will be supplied clean and disinfected.

6. STUDY PROCEDURES – METHODS

## 6.1 Study Location and Medical Team

This protocol is submitted to Rwanda National Ethics Committee. The study center will be located in Rwanda Military Hospital.

## 6.2 Informed Consent Procedure

- - In obtaining and documenting informed consent, the investigator should comply with the applicable regulatory requirements, and should adhere to GCP, HIPAA and the ethical principles that have their origin in the Declaration of Helsinki
  - Prior to the beginning of the trial, the investigator should have the written informed consent form and any other written information approved by the National Ethical Committee before it is provided to subjects
  - The written informed consent form and any other written information to be provided to subjects should be revised whenever important new information becomes available that may be relevant to the subject’s consent. Any revised written informed consent form, and written information must be approved by the Ethic Committee before it is made available for subject signature. The subject should be informed in a timely manner if new information becomes available that may be relevant to the subject’s willingness to continue participation in the trial. The communication of this information should be documented
  - Neither the investigator, nor the trial staff, should coerce or unduly influence the subject to participate or to continue to participate in a trial. He will also testify of his agreement by a signature on the same ICF
  - The investigator, or a person designated by the investigator, should fully inform the subject of all pertinent aspects of the trial including the Ethical committee approved written informed consent
  - Before informed consent may be obtained, the investigator, or a person designated by the investigator, should provide the subject ample time and opportunity to inquire about details of the trial and to decide whether or not to participate in the trial. All questions about the trial should be answered to the satisfaction of the subject
  - Prior to a subject’s participation in the trial, the Ethical Committee approved written informed consent form should be signed and personally dated by the subject or by the subject's legally acceptable representative, and by the person who is authorized to conduct the informed consent discussion
  - Prior to participation in the trial, the subject should receive a copy of the signed and dated written informed consent form and any other written information provided to the subjects.
  - During a subject’s participation in the trial, the subject should receive a copy of the signed and dated consent form updates and a copy of any amendments to the written information provided to subjects.
  - Subject must provide informed consent and sign and date with his hand writing an Informed Consent Form (ICF) prior to any study related procedures being performed. The person reviewing the ICF with the subject must also sign and date the ICF. Each of the signers must sign and date the Form in the presence of the other signer.

**If subject is unable to comprehend and sign the Consent Form, subject must not be enrolled in the study.**

## 6.3 Study Schedule of Events

The following represents the study schedule of events

1. The procedure will be performed in Rwanda Military Hospital
2. **Inclusion Exclusion Criteria** – Subjects will be evaluated for inclusion in the study according to inclusion and exclusion criteria. Subject which do not meet the criteria will be offered circumcision out of the study procedures and records
3. **Informed Consent** – Potential candidate for enrollment to the study will be consented
4. **Randomization -** Subjects who meet all of the inclusion exclusion criteria will be randomly assigned to one of the study arms – Arm 1, Arm 2 or Arm 3

**Note -** The PrePex Operators and Assistants must be formally trained with the most up to date training program and certified as PrePex Operator and Assistants in a formal PrePex training program to take place in Kigali, Rwanda. In addition there may be training refreshment during the procedure of the first 20 procedures of the study.

1. **Circumcision** -

**Procedure:**

After assessment of eligibility and after the subject has signed the informed consent form, the subject will be enrolled in the study.

A **standard PrePex procedure** is described below:

The procedure will be carried out in a clean non-sterile environment. The subject will undergo sizing of the penis sulcus with the PrePex Sizing Plate. The penis will be cleaned by red Povidone-Iodine solution or other disinfection solution (Chlorahexidine, etc.) with the foreskin stretched backwards to expose the inner skin for the disinfection solution. Then the foreskin will be dried with a dry gauze. The Operator will then mark the circumcision line with a clean skin marker and then the Assistant will open the corresponding sized package of the PrePex device, and will load the Elastic Ring on to the Placement Ring. Then, Lidocaine 5% dermal cream will be applied on the inner foreskin. The Placement Ring with the Elastic Ring will be placed on the penis shaft and the foreskin tip will be stretched open to the sides by the operator hands, the operator may select to use a dry gauze to affirm the grip. Then, the Inner Ring will be applied through the stretched foreskin and over the glans penis (hereinafter, "glans") so that it will be placed fixed over the sulcus behind the glans (the base of the glans). At this point, the foreskin around the inner ring is held tight by the Assistant, and the Placement Ring and Elastic-Ring are approximated to the Inner Ring by the Operator. The foreskin is then adjusted to fit the circumcision marking line to the Elastic-Ring. Then, the Elastic-Ring is released from the Placement Ring on to the Inner Ring groove, initiating homeostasis. The procedure is then completed. Medication based on 400mg Ibuprofen is given to the subject to use at home if needed. The subject will then take part in a formal discharge session in a class room, where he will be instructed to return for a follow up visit and in any non sustained situation and to take painkillers in case of pain. The device will remain in situ for 7 days, at which the subject will return for a removal visit (i.e. if placed on Monday, removed on the following Monday). In case subjects arrive on day 5 or 6 and require removal of the device and foreskin, it is for the medical decision of the center managing physician to perform the removal if he/she thinks the removal is safe at this day. Those subjects will be followed for the procedure safety and efficacy. The foreskin is removed using sterile scissors, the Elastic Ring is removed using a #10 scalpel (surgical blade), and then the Inner Ring is extracted using a spatula or fingers, depending on the thickness of the foreskin. The area might be compressed with gauze for 30 seconds to avoid oozing and clear exudates. Following the removal process, the circumcision area will be dressed with a non-adherent sterile pad for 2 days, the subject will receive one dressing pad for home to change in case the dressing gets wet. The subject will then take part in a formal discharge session in a class room, where he will be instructed to turn to his local health center in any non sustained situation. Following the 2 days (day 9) the subject will remove the dressing on his own at home. The subject will be instructed to return in any non sustained situation, regardless of the follow-up visit.

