**Study arms:**

The subjects will be randomized into 3 study arms, using a randomization table and sealed envelopes:

**Arm 1:** A control arm – subjects instructed to follow the current hygiene instructions of standard washing with soap and water during a daily shower. They will get a soap to take home and will be questioned daily to make sure they followed the cleaning instructions.

They might be requested to wash themselves at the hospital before the actual Removal visit starts.

**Arm 2:** subjects instructed to clean the foreskin with soapy water once a day using a syringe.

They will get a soap and required accessories to take back home and will be questioned daily to make sure they followed the instructions.

Subjects may be requested to wash themselves at the hospital before the actual Removal visit starts.

**Arm 3:** subjects instructed to clean the foreskin with diluted chlorhexidine (1%) once a day using a syringe. They will get chlorhexidine in tubes and required accessories to take back home and will be questioned daily to make sure they followed the instructions.

Subjects may be requested to wash themselves at the hospital before the actual Removal visit starts.

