***Statistical Analysis:***

All data will be presented via descriptive statistics. Binary data such as adverse events success/fail criteria will be presented as a count and percentage together with an exact 95% confidence interval. Adverse event rates will be compared descriptively with the reported rates of similar treatments. Continuous data will be represented by a mean, standard deviation, median, minimum and maximum together with 95% confidence intervals for the means.

Study Flow

Screen 120 candidates

100 enrolled subjects

Randomization

Arm 1 -33 subjects

- Standard PrePex
- General hygiene instructions
- Foreskin hygiene general instructions – daily shower

Arm 2 -33 subjects

- Standard PrePex
- General hygiene instructions
- Foreskin specific hygiene instructions – daily soapy water with syringe
- **Follow up visits days 3, 5 & 7**
- Subject questionnaires
- Odor tests by 3 Blinded smellers
- Partner questionnaire – on days 3, 5 & 7
- Removal on day 7
- A random sample of subjects were evaluated a second time on day 7
- Safety - AEs

Arm 3 – 33 subjects

- Standard PrePex
- General hygiene instructions
- Foreskin specific hygiene instructions - daily chlorhexidine with syringe

|  | **Randomization & Screening Visit** | **Applying Visit** |  |  | **Removal Visit** |
| --- | --- | --- | --- | --- | --- |
| **Visit #** | **1** | **2** | **3** | **4** | **5** |
| **Day (D)/week (w)** | **–7 to D0** | **D0** | **D3** | **D5** | **D7** |
| Informed consent | X |  |  |  |  |
| Randomization | X |  |  |  |  |
| Inclusion/exclusion criteria | X |  |  |  |  |
| Medical history & Demography | X |  |  |  |  |
| Current medication including pain killers | X | X |  |  | X |
| Genital examination and potential pictures | X | X | X | X | X |
| Device apply |  | X |  |  |  |
| Foreskin Removal |  |  |  |  | X |
| Device Removal |  |  |  |  | X |
| Subject's subjective pain, tingling and discomfort evaluation |  | X | X | X | X |
| Expected Side effects and AE |  | X | X | X | X |
| Smellers test |  | X | X | X | X |
| Questionnaires for patients & for sub group female partners (between days 5-6) |  |  | X | X | X |
| Statistical analysis of data |  |  |  |  |  |

Table of Contents

[Study Synopsis 2](#__RefHeading___Toc344626056)

[Schedule of Events 8](#__RefHeading___Toc344626057)

[1. Clinical background 12](#__RefHeading___Toc344626058)

[2. STUDY OBJECTIVES AND PURPOSE 15](#__RefHeading___Toc344626059)

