**Exclusion Criteria:**

- Active genital infection, anatomic abnormality or other condition, which in the opinion of the investigator prevents the subject from undergoing a circumcision
- Subject with the following diseases/conditions: phimosis, paraphimosis, warts under the prepuce, torn or tight frenulum, narrow prepuce, hypospadias, epispadias
- Known bleeding / coagulation abnormality, uncontrolled diabetes, by questionnaire
- Subject who have an abnormal penile anatomy or any penile diseases
- Subject that to the opinion of the investigator is not a good candidate
- Subject does not agree to anonymous video and photographs of the procedure and follow up visits.

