**PrePex MC**

**Classification of Adverse Events and Device Hazards**

| **Adverse**  **Event** | **Description** | **Severity** | **Code** |
| --- | --- | --- | --- |
| **A. During Placement** | | | |
| Pain | Pain score of 8 or more not requiring anesthesia  Requires anesthesia  Not controlled by additional anesthesia | Mild  Moderate  Severe | APP1  APP2  APP3 |
| Difficulty in applying the device | Could not apply device; determined as contra indicated; no harm to tissue or subject  Had to push unusually hard, but no harm to tissue or subject and no change to procedure  The device cut through the foreskin, with or without minor bleeding, No change in procedure  The device cut through the foreskin, with or without minor bleeding, and requiring a change to surgical method  The device cut through the foreskin, causing significant bleeding and requiring a change to surgical method | No AE  No AE  Mild  Moderate  Severe | --  --  ADD1  ADD2  ADD3 |

| **Adverse**  **Event** | **Description** | **Severity** | **Code** |
| --- | --- | --- | --- |
| **B. While Wearing the Device** | | | |
| Pain / Discomfort | Not requiring intervention beyond painkiller or anesthetic cream  Requiring early device removal by PrePex Operator or by client  Requiring early device removal and anesthesia  Not controlled by device removal or additional anesthesia | Not AE  Mild  Moderate  Severe | --  BWP1  BWP2  BWP3 |
| Device displacement / spontaneous detachment | Device displacement with no clinical consequences  Complete spontaneous detachment, or patient removed device himself with no adverse clinical consequences  Device displacement requiring re-placement  Device displacement requiring surgical intervention  Displacement or detachment and penile damage present | Not AE  Mild  Moderate  Severe | --  BDD1  BDD2  BDD3 |
| Early device removal (i.e. 4 days or less with the device) | Device removed due to pain, swelling or bleeding  Device removed due to pain, swelling or bleeding requiring surgical intervention  Device removed and penile damage present | Mild  Moderate  Severe | BER1  BER2  BER3 |
| Edema | More edema than usual but not causing any discomfort to the patient  Moderate edema causing the patient discomfort, though managed with conservative measures  Severe edema, causing the patient discomfort, uncontrolled with conservative measures | Mild  Moderate  Severe | BED1  BED2  BED3 |

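### Men are randomised before device sizing and placement, so any man whose device cannot be applied is lost after allocation: a minor loss, nearly free to avoid

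*Protocol*

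**What the plan says.** Protocol 6.3 lists the steps in order: criteria, consent, randomisation, circumcision. At the randomisation step, "Subjects who meet all of the inclusion exclusion criteria will be randomly assigned to one of the study arms". The schedule table in the Synopsis gives the same order. Visit 1 (day -7 to D0) is headed "Randomization & Screening Visit", and the device is applied at Visit 2 (D0). Allocation uses a randomisation table and sealed envelopes (Synopsis, Study arms).

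Enrolment comes before the procedure: "After assessment of eligibility and after the subject has signed the informed consent form, the subject will be enrolled in the study". Sizing is the first act within that procedure: "The subject will undergo sizing of the penis sulcus with the PrePex Sizing Plate". The schedule has a row "Genital examination and potential pictures" marked at Visit 1, but no row for sizing.

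The criteria in 4.2 and the Synopsis exclude named conditions ("phimosis, paraphimosis, warts under the prepuce, torn or tight frenulum, narrow prepuce, hypospadias, epispadias"), other abnormal anatomy, and men whom the investigator considers poor candidates. None refers to device size or fit.

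The adverse event classification, part A (During Placement), includes the outcome "Could not apply device; determined as contra indicated; no harm to tissue or subject" and grades it as no adverse event. Section 8.3.2.1 restricts the intent-to-treat population to men in whom the device was placed.

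**The concern.** A man can be assigned to an arm up to a week before anyone tries the device on him. If it cannot be applied, he has an allocation but nothing to analyse: the primary endpoint is odor while the device is worn, and he never wears it. No analysis rule can recover that reading, whereas a different order of steps would prevent the loss.

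Three things are at stake:

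- **Numbers.** The sample size of 33 per arm only just reaches 80% power. The flow chart enrols 100 men for a target of at least 100 evaluable, and its slack (120 screened) lies before enrolment.
- **The randomised comparison.** Under 8.3.2.1 the set called intent-to-treat is the randomised set less the men not placed.
- **Knowledge of the arm.** In an open-label trial, the decision to place may be made by someone who could know the allocation.

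**Working it through.** **Order of events.** Criteria and randomisation are at Visit 1. Sizing and placement are at Visit 2. Membership of the intent-to-treat set depends on placement. The loss after allocation follows from these provisions together. The protocol has no explicit rule for a man found unsuitable at placement.

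**The plan's own sample size.** Inputs from 8.3 and 8.3.1: d = 0.7, 80% power, 5% level, two-sided, two-sample t-test.

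- Normal approximation: n = 2 × ((1.960 + 0.842) / 0.7)² = 32.04, rounded up to 33 per arm.
- Exact t-test: n = 33.02, and power at 33 per arm is 79.97%.

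The stated 33 per arm reproduces.

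**How often might it happen?** The protocol gives no rate of failed application. The nearest figure is in its summary of the nurse study at the same hospital, where all 590 enrolled men were circumcised. With 0 failures in 590:

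- one-sided 95% upper bound = 1 − 0.05^(1/590) = 0.51%
- two-sided 95% upper bound = 1 − 0.025^(1/590) = 0.62%

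At the one-sided bound, the expected loss among 100 randomised men is 100 × 0.0051 = 0.5 of a man. The chance of losing at least one is 1 − (1 − 0.00506)^100 = 40%.

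The bound carries a caveat. The summary does not say whether sizing came before enrolment in that study, and if it did, men rejected at sizing would not be among the 590.

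**What a loss costs.** Power of the pairwise t-test at d = 0.7, with noncentrality 0.7 × √(n₁n₂/(n₁+n₂)):

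| Arms compared | Men lost from the pair | Power |
| --- | --- | --- |
| 33 v 33 | 0 | 80.0% |
| 33 v 32 | 1 | 79.3% |
| 32 v 32 | 2 | 78.7% |
| 31 v 31 | 4 | 77.4% |

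One loss costs about 0.6 percentage points. It cannot take both arms of a pair to 32.

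**Sensitivity to the caveat.** If the 590 were already selected by sizing, the true rate could be higher. At an assumed 1%, 1 man in 100 would be expected lost, and at an assumed 5%, 5 men. At 5% lost evenly, 33 × 0.95 = 31.35 men per arm remain and power is 77.9%. Nothing in the documents supports a rate that high.

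**The case against.** The case against giving this much weight is strong, and most of it stands.

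- **The classification entry is about applying the device, not sizing.** It appears under difficulty in application, and the procedure uses sizing to choose the package. No text says that a man is rejected at sizing. This stands, and it means that sizing earlier need not detect a failed application.
- **The classification is a general form.** A reader might infer that the protocol expects some randomised men to be found unsuitable. It does not say so. The same form covers events six weeks or more after removal, although this trial has no follow-up after the removal visit. Listing an outcome is not forecasting it.
- **Much unsuitability is already screened out.** The anatomical exclusions, the investigator's discretion and the Visit 1 genital examination all act before allocation. Nothing requires the Sizing Plate to be used then, but the remaining group is small.
- **Lack of reserve is only partly right.** Sections 4.1 and 8.3.2 state floors (at least 100 evaluable men, at least 33 per arm), which would allow further recruitment. The flow chart nevertheless shows 100 enrolled, and no replacement rule is given.
- **Bias.** A reader might infer that staff who know the arm could select whom to place. All arms receive the same device and differ only in washing afterwards, so fit has no evident link to arm. The documents do not say that the operator is told the allocation. The opportunity exists, but nothing suggests that it would matter much.

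What remains is the sequence itself: allocation comes first, and a man who is not placed is lost to the analysis.

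**Conclusion.** The point holds as a minor one. The protocol randomises before it establishes that the device can be applied, has no fit criterion, and analyses only placed men, so any failed application is a loss after allocation. No stated figure is wrong and no passages conflict.

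If the nurse study's experience carries over, the loss is at most about one man per 100. One loss moves pairwise power from 80.0% to about 79.3%. That size rests on the 590 of 590 result, on the unstated timing of sizing in that study, and on the plan's own t-test assumptions. The documents do not support a reading in which the trial is materially underpowered or biased by this. The reason to act is that the loss can be avoided at almost no cost.

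**What to change.** There are two ways to do it, and the second is better.

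1. **Check fit before allocation.** Do the sizing at the genital examination already scheduled at Visit 1, before the envelope is opened. Add device fit to the criteria in 4.2 and the Synopsis, and keep sizing at placement as confirmation. This removes men whose unsuitability shows at sizing, but may miss failures that appear only on application.

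2. **Open the envelope on D0, once the device is in place and before the discharge instructions.** The arms do not diverge until washing begins, so nothing before that moment needs the allocation. Every randomised man is then a placed man, the set defined in 8.3.2.1 coincides with the randomised set, and the arm is unknown when the decision to place is made. The edits are to the order of steps in 6.3, the randomisation row and Visit 1 heading of the schedule table, and the flow chart.

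Neither option adds visits or patients. The cost is that a few men are turned down before allocation instead of after it. Under the second option, arm-specific supplies and instructions must be ready to hand out on D0. Both options change only when allocation happens relative to the fit check, not how the device is used.
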